## Abstract

**Introduction::**

Misfolded aggregated proteins and neuroinflammation significantly contribute to amyotrophic lateral sclerosis (ALS) pathogenesis, hence representing therapeutic targets to modify disease expression. Rapamycin inhibits mechanistic target of Rapamycin (mTOR) pathway and enhances autophagy with demonstrated beneficial effects in neurodegeneration in cell line and animal models, improving phenotype in SQSTM1 zebrafish, in *Drosophila* model of ALS-TDP, and in the TDP43 mouse model, in which it reduced neuronal loss and TDP43 inclusions. Rapamycin also expands regulatory T lymphocytes (Treg) and increased Treg levels are associated with slow progression in ALS patients.

Therefore, we planned a randomized clinical trial testing Rapamycin treatment in ALS patients.

**Methods::**

RAP-ALS is a phase II randomized, double-blind, placebo-controlled, multicenter (8 ALS centers in Italy), clinical trial. The primary aim is to assess whether Rapamycin administration increases Tregs number in treated patients compared with control arm. Secondary aims include the assessment of safety and tolerability of Rapamycin in patients with ALS; the minimum dosage to have Rapamycin in cerebrospinal fluid; changes in immunological (activation and homing of T, B, NK cell subpopulations) and inflammatory markers, and on mTOR downstream pathway (S6RP phosphorylation); clinical activity (ALS Functional Rating Scale-Revised, survival, forced vital capacity); and quality of life (ALSAQ40 scale).

**Discussion::**

Rapamycin potentially targets mechanisms at play in ALS (i.e., autophagy and neuroinflammation), with promising preclinical studies. It is an already approved drug, with known pharmacokinetics, already available and therefore with significant possibility of rapid translation to daily clinics. Findings will provide reliable data for further potential trials.

**Ethics and dissemination::**

The study protocol was approved by the Ethics Committee of Azienda Ospedaliero Universitaria of Modena and by the Ethics Committees of participating centers (Eudract n. 2016-002399-28) based on the Helsinki declaration.

## Introduction

1

Protein aggregates into neurons and glial cells are common features of amyotrophic lateral sclerosis (ALS) pathology, and have a key role in ALS initiation and progression: TDP43 proteinopathy is a hallmark of >95% of sporadic/nonmutated ALS.^[1,2]^ Protein degradation machinery and autophagy have a crucial role in dealing with misfolded aggregated proteins.^[3]^ In ALS several genes (UBQLN2, SQSTM1, OPTN, VCP, TBK1) have strong links with protein degradation pathways as their products contribute to recruitment of ubiquitinated proteins to the autophagosome. Autophagy is also required for the removal of aberrant stress granules involved in ALS pathology ^[4]^ and for downregulation of inflammasome activity, which is activated in response to cellular inclusions formation.^[5]^ TBK1, OPTN, and SQSTM1 converge on autophagy and neuroinflammation, suggesting that compounds which affect both pathways may be promising.^[1]^ A recent paper showed a function for C9orf72 at lysosomes, with impaired responses of mechanistic Target of Rapamycin (mTOR) Complex 1 (mTORC1) signaling to changes in aminoacid availability after depletion of either C9orf72 or SMCR8.^[6]^

mTOR integrates signals to elicit critical outputs, including growth control, protein synthesis, gene expression, and metabolic balance. ^[7]^ The action of Rapamycin is based on mTORC1 inhibition. mTORC1 targets regulatory proteins in cell signaling and regulates autophagy by inhibiting the unc-51-like kinase 1 complex. Inhibition of mTORC1 by Rapamycin stimulates autophagy, through the formation of autophagosome from the phagophore.

mTOR acts on homeostasis of T cells. Indeed, naive CD4+ T cells can develop into TH1, TH2, or TH17 effectors using pathways promoted by mTOR. Conversely, mTOR inhibits the induction of regulatory T lymphocytes (Treg), cells that downregulate immune activation. Inhibition of mTORC1 by Rapamycin expands Tregs and, in mSOD1 mice, increased Tregs and induction of M2 microglia (with anti-inflammatory properties) were associated with stable phase of disease. In ALS patients, blood percentage of Tregs inversely correlated with progression rate, and FoxP3 levels were early predictors of ALS progression and survival.^[8]^ Thus, Tregs may be considered important therapeutic targets in ALS addressed by Rapamycin.

Rapamycin has been tested in several neurodegeneration models because it is an mTOR-dependent autophagy activator, and accelerates the removal of abnormal accumulation of aggregated proteins ^[9,10]^ with beneficial effects.^[7]^ Rapamycin administration exerted a beneficial effect in several cell lines,^[9,11–13]^ and in several ALS animal models, improving motor and cognitive phenotype.^[14–18]^

Based on these premises, we are going to perform a clinical trial in ALS patients with Rapamycin, a drug that enhances autophagy, facilitates TDP43 clearance, and regulates immune responses.

## Methods

2

### Objectives

2.1

The primary objective is to assess whether different Rapamycin doses increase Treg number in ALS patients compared with the control arm.

Secondary objectives include the following:

1.*Assessment of Rapamycin safety and tolerability in a cohort of ALS patients*: occurrence of adverse events (AEs), changes on clinical examination including vital signs and weight, and laboratory examinations (biochemistry, hematology and urinalysis) will be registered throughout the entire study duration.2.*Biological assessment*: To analyze Rapamycin efficacy in inhibiting MTOR pathway, by quantifying the phosphorylation of the S6 ribosomal protein (S6RP) comparing baseline and weeks 8, 18 (treatment end), 30, and 54 between Rapamycin arms and placebo arm. To identify changes in activation and homing capabilities of different T, B, NK cell subpopulations comparing baseline and weeks 8, 18 (treatment end), 30, and 54 between Rapamycin arms and placebo arm. To study Rapamycin effects on different biomarkers (including peripheral and CSF biomarkers, that is, creatinine and albumin, CK, vitamin D, plasma/CSF neurofilament heavy/light chain protein) comparing baseline and week 8, 18 (treatment end), 30, and 54 between Rapamycin arms and placebo arm. To identify Rapamycin-induced changes in inflammatory status, by the molecular analysis of the inflammasome system baseline and week 8, 18 (treatment end), 30, and 54 between Rapamycin arms and placebo arm. To assess Rapamycin capacity to pass through blood–brain barrier (BBB).3.*Clinical assessment*: to assess changes in Amyotrophic Lateral Sclerosis Functional Rating Scale (ALSFRS)-Revised from baseline to weeks 4, 8, 12, 18, 30, 42, and 54 in placebo and treatment arms; overall survival from randomization to date of documented death or tracheostomy; survival rate at weeks 18, 30, 42, and 54; forced vital capacity (FVC) score from baseline to weeks 4, 8, 12, 18, 30, 42, and 54.4.Quality of life assessment: ALSAQ-40 from baseline to weeks 8, 18, 30, and 54 in treatment and placebo arms.

### Design of the study

2.2

This is a multicenter, randomized, double-blind, placebo-controlled, phase II clinical trial. It has been designed following the guidelines on clinical investigation of medicinal products for the treatment of ALS provided by the European Medicines Agency and adopted by the Agenzia Italiana del Farmaco. The protocol has been discussed and revised according to the suggestions of the Data Safety and Monitoring Board (DSMB). The DSMB includes:

[name], University of Toronto.[name], University of Milan.[name], IRCCS Foundation “Carlo Besta” Neurological Institute, Milan.[name], IRCCS “Mario Negri” Institute, Milan.

The protocol (version 2, April 21, 2017) has been designed adhering to the *Standard Protocol Items for Randomized Trials (SPIRIT)*. The trial has been registered on EU Clinical Trials Register (https://www.clinicaltrialsregister.eu/ctr-search/trial/2016-002399-28/IT) and on Clinicaltrials.gov (https://clinicaltrials.gov/ct2/show/NCT03359538?term=rapamycin&cond=Amyotrophic+Lateral+Sclerosis&rank=1)

Figure 1 shows the design of the study.

**Figure 1 F1:**
[figure not shown]
design of the study RAP-ALS.

### Eligibility criteria

2.3

Patients affected by probable (clinically or laboratory supported) or definite ALS ^[19]^ will undergo screening procedures that must be completed during the 14-day screening period. All patients must adhere to inclusion and exclusion criteria (Table 1) through clinical evaluation and laboratory and instrumental assessment. Screening assessments include blood sampling, biochemical and pregnancy evaluations (for fertile females) which will be performed in the site's local laboratory, general and neurological examinations, MRC, ALSFRS-R, chest radiography and ECG, and spirometry.

**Table 1 T1:**
[figure not shown]
Inclusion and exclusion criteria for RAP-ALS trial.

### Randomization

2.4

Eligible patients will be randomized strictly sequentially, according to a randomization list prepared by the Biostatistician of the University of Modena.

All patients will receive a unique patient identification number at screening visit when signing the informed consent and before any study procedures are performed. Sixty-three patients will be randomized in the following 3 groups:

1.21 patients will receive Rapamycin 2 mg/m^2^/d + riluzole.2.21 patients will receive Rapamycin 1 mg/m^2^/d + riluzole3.21 patients will receive placebo + riluzole

### Stratification

2.5

Randomization will be performed online. Patients will be stratified according to ΔFS (</≥0.7),^[20]^ with 1:1:1 allocation in 3 treatment arms (Rapamycin 1 mg/m^2^/d; Rapamycin 2 mg/m^2^/d, placebo). The investigators will randomize patients directly online. Treatment will begin within 14 days from randomization. In case of discontinuation from the study, the randomization number will not be reused.

### Experimental drug preparation

2.6

Pfizer S.r.L. gave the active treatment (Rapamycin) free of charge. Euromed Clinical Supply Services (ECLISSE) (Cantù (Como), Italy; http://www.css.euromed.it/en/) prepared the active formulation and the placebo. The active powder and the investigational drug have been produced complying the Good Manufacturing Practices of the European Union for active pharmaceutical ingredients and ICH Q7A guidelines. Verum and placebo are identical and unrecognizable tablets by form size, weight, and color, and will be indistinguishable to patients and neurologists.

### Treatment and blindness

2.7

This study is a phase II randomized, double-blind, placebo-controlled, multicenter, clinical trial (RCT) to test Rapamycin in ALS patients. The study will include 63 ALS patients (EL Escorial Revised Criteria, sporadic and familial) with 1:1:1 allocation in 3 groups of 21 subjects each; treatment will be double blinded, and will last 18 weeks. Active treatment will include oral Rapamycin at 1 mg/m^2^/d or 2 mg/m^2^/d.

Rapamycin levels will be regularly measured and revealed only to an independent monitor, who will input Rapamycin levels on a separate eCRF, and on the basis of that value dosing changes may be performed at each treatment dispensation directly through eCRF (and blinded to caring neurologists who will supply bottles identified by a number and corresponding to different blinded doses) to keep Rapamycin levels from 4 to 12 ng/mL. Computerized randomization will be stratified by ΔFS (</≥0.7).

After treatment end (week 18) patients will be followed up for further 36 weeks. This large period of follow-up has the aim to assess potential late side effects of the treatment and to assess whether eventual biological or clinical effects of the treatment with respect to placebo, may last after drug discontinuation.

For the first 10 patients enrolled, clinical and biological safety assessments will be performed every week for the first month, and then every 2 weeks until the end of treatment. For the remaining 53 patients clinical assessments will be performed every 2 weeks for the first month, and then every 4 weeks during treatment duration.

If at either the interim or the final analyses safety concerns will arise, the trial will be stopped and all available data will be reviewed by the Study Steering Committee.

Table 2 shows study procedures to be undertaken.

**Table 2 T2:**
[figure not shown]
study flowchart (excluding the first 10 patients, for whom additional visits are scheduled).

### Concomitant treatments

2.8

Patients must have been treated for a minimum of 1 month with a stable dose of riluzole (100 mg/d) at baseline. Safety issues related to riluzole will be managed according to usual practice.

Treatment of ALS impairments (nutrition, respiration, motricity, communication) will be done with a multidisciplinary approach and accordingly to EFNS Guidelines for ALS patients’ management.^[21]^

As for prohibited treatments Rapamycin is known to be a substrate for both cytochrome P-450 3A4 (CYP3A4) and p-glycoprotein (P-gp). Inducers of CYP3A4 and P-gp may decrease Rapamycin concentrations, whereas inhibitors of CYP3A4 and P-gp may increase Rapamycin concentrations. Concomitant use of strong inducers is not recommended, whereas it is forbidden concomitant use of strong inhibitors of CYP3A4 and P-gp.

Alternative agents with lesser interaction potential with Rapamycin should be considered.

Immunosuppressants may affect response to vaccination. Therefore, during treatment with Rapamycin, vaccination may be less effective. Because grapefruit juice inhibits the CYP3A4-mediated metabolism of Rapamycin, it will be not allowed to take with or be used for dilution of Rapamycin.

### Outcomes

2.9

The primary outcome is represented by the change from baseline to week 18 in Treg number in ALS patients treated with Rapamycin compared with the control arm.

Secondary outcomes are as follows:

1.*Safety*: Occurrence of AEs and per-treatment arising changes in physical examination, vital signs (blood pressure, pulse rate, and body temperature), body weight, and clinical laboratory tests (biochemistry, hematology). MedDRA dictionary is going to be used for reporting.2.*Rapamycin levels in CSF* at week 18 (high-performance liquid chromatography (HPLC) with mass spectrometry (MS) (LC–MS/MS).3.Change from baseline to each time point (weeks 8, 18, 30, and 54) of the phosphorylation of the S6 ribosomal protein *(S6RP)* comparing Rapamycin arms and placebo arm.4.Change from baseline to each time point (week 8, 18, 30, and 54) of the activation and homing capabilities of different *T, B, NK cell subpopulations* comparing Rapamycin arms and placebo arm.5.Changes from baseline to each time point (weeks 8, 18, 30, and 54) in different *biomarkers* (including peripheral and CSF biomarkers that is, creatinine and albumin, CK, vitamin D, plasma/CSF neurofilament heavy/light chain protein) comparing Rapamycin arms and placebo arm.6.Changes from baseline to each time point (weeks 8, 18, 30, and 54) in *inflammatory status (molecular analysis of the inflammasome system)* comparing Rapamycin arms and placebo arm.7.Change from baseline to each time point (weeks 4, 8, 12, 18, 30, 42, and 54) of *ALSFRS-R.*8.*Survival* defined as the time from randomization to the date of documented death or tracheotomy.9.Survival rate at weeks 18, 36, and 54.10.*Change of FVC* from baseline to each time point (weeks 4, 8, 12, 18, 30, 42, and 54).11.Absolute and relative change from baseline in *ALSAQ-40* (Amyotrophic Lateral Sclerosis Specific Assessment Questionnaire at weeks 4, 8, 12, 18, 30, 42, and 54).

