### Sample size calculation

2.13

The sample size has been estimated considering as the primary outcome measure the proportion of positive response (Tregs number increase) at treatment end (18 weeks) in patients treated with Rapamycin versus placebo.

ALS patients have a slight reduction of Treg% (mean±SD: 2.1 ± 0.7) with respect to healthy controls (2.6 ± 0.6) (Treg% calculated on total lymphocytes; normal values of total lymphocytes: 1000–4500/μL; normal values of total Treg: 71.5 ± 17/μL).^[22]^

Slowly progressive ALS patients have a number of Tregs that is equal to healthy controls, whereas fast progressors have 31% fewer Tregs than slowly progressing patients, and Treg % is inversely correlated with the rate of disease progression.^[8]^ These data indicate that ALS patients have 60 ± 17 Treg/μL (fast progressors: 49.3 Treg/μL; slow progressors: 71.5 Treg/μL). As a result, a “positive response” can be considered an increase of the proportion of Tregs by ≥30%. The null hypothesis is that Rapamycin does not increase significantly the proportion of positive responses in treated patients at 18 weeks compared with their baseline stage and to placebo group. The alternative hypothesis is that Rapamycin determines a proportion of positive responses in ≥50% of treated patients compared with a maximum 5% of patients in the placebo group. The study has been designed to reject the null hypothesis with an alpha error of 0.025 (to take into account a multiple comparison with a control arm) and a power of 0.80. For this purpose, a sample of 54 patients randomized in 3 treatment arms would be needed. Considering an average drop out of 15% then a recruitment of 63 patients will be necessary.

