### Statistical analyses

2.14

Separate analyses will be performed in

1.all randomized subjects receiving ≥1 dose of study medication (intention-to-treat population);2.all randomized subjects excluding protocol deviations (per protocol, PP population).

Descriptive statistics will be performed comparing the 2 groups of Rapamycin treatment and placebo. Continuous variables will be described using mean and standard deviation or median and interquartile range; categorical variables will be described as counts and percentages.

Safety analysis will be performed in all subjects receiving ≥1 dose of the experimental drug. All AEs, SAEs, and AEs leading to treatment discontinuation will be recorded according to ICH Guidelines, listed, and compared in the treatment arms at any follow-up visit and at the end of the study.

Differences in tracheostomy-free survival (Kaplan–Meier method) between the treated groups and placebo group will be compared using the log-rank test. Cox's proportional hazard model would be used to adjust for any possible unbalanced prognostic factors. Statistical significance will be set at .05 level for a 2-tailed test. Missing data will be handled using the last observation carried forward.

Immune response to Rapamycin will be analyzed as the difference in positive response to Rapamycin (mean Tregs increase >30%) between the placebo group and the Rapamycin groups. This will be calculated with the use of Treg data obtained at baseline and at week 18.

We will compare the mean values of S6RP phosphorylation, of different T, B, NK cell subpopulations, of biomarkers, inflammasome, cytokines, comparing baseline and treatment end (18 weeks) between Rapamycin and placebo arm. Mean differences in plasma concentrations from baseline to week 18 in the 2 treatment arms will be calculated and compared using *t* test or Wilcoxon–Mann–Whitney test.

The mean change over time for the same variables as above will be assessed using repeated measures ANOVA, with treatment as between-subjects factor and time as within-subjects factor. Different models will be used, each with a different biomarker of activity as the dependent variable. Models will be adjusted for any unbalanced distribution of the main prognostic factors (e.g., age) between the 2 treatment arms.

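### The primary outcome is a continuous change in Treg number in sections 2.1 and 2.9 but a responder proportion in 2.13 and 2.14, and the response itself is defined inconsistently

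*Protocol article*

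**What the plan says.** - **Sections 2.1 (Objectives) and 2.9 (Outcomes).** The objective is an increase in Treg number. The outcome is the change in that number over the treatment period: "The primary outcome is represented by the change from baseline to week 18 in Treg number in ALS patients treated with Rapamycin" against the control arm.
- **Section 2.13 (Sample size calculation).** The primary outcome measure is now "the proportion of positive response (Tregs number increase) at treatment end (18 weeks) in patients treated with Rapamycin versus placebo". A positive response "can be considered an increase of the proportion of Tregs by ≥30" per cent. The null and alternative hypotheses both concern responder proportions. The alternative is that "Rapamycin determines a proportion of positive responses in ≥50% of treated patients compared with a maximum 5% of patients in the placebo group", with "an alpha error of 0.025 (to take into account a multiple comparison with a control arm) and a power of 0.80". The result is 54 evaluable patients (18 per arm) and 63 recruited.
- **Section 2.14 (Statistical analyses).** Immune response "will be analyzed as the difference in positive response to Rapamycin (mean Tregs increase >30%) between the placebo group and the Rapamycin groups", using baseline and week 18 data. No test is named for this. A separate paragraph compares means of S6RP phosphorylation, lymphocyte subsets and other markers, naming the t test or Wilcoxon–Mann–Whitney. Repeated measures ANOVA follows for the same variables. Tregs are not named in that part, and 2.9 lists the lymphocyte subsets as a separate secondary outcome.

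**The concern.** Two different variables are each called primary. One is a continuous change. The other is a yes/no classification of the same measurements at a 30% cut. They answer different questions and can disagree: a modest rise shared by most patients can show clearly in the mean while few patients cross 30%.

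The response rule is also unsettled in three ways, each of which can change who counts as a responder:

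1. **Number or proportion.** Section 2.13 uses both within one derivation. Treg percentage there is taken on total lymphocytes, so count and percentage diverge when lymphocytes change.
2. **At least 30% (2.13) or more than 30% (2.14).**
3. **A per-patient rule (2.13) or a mean increase (2.14).** A mean belongs to a group and cannot classify a patient.

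The trial exists to show target engagement and to inform a later efficacy trial. A primary result that depends on which section is followed weakens that purpose.

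**Working it through.** **1. The definitions side by side**

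| Section | Variable | Type | Hypothesis | Sample size | Test named |
|---|---|---|---|---|---|
| 2.1, 2.9 | Change in Treg number | Continuous | None | None | None assigned as primary |
| 2.13 | Patients with a Treg rise of at least 30% | Binary | Yes | 54, then 63 | None |
| 2.14 | Positive response, mean rise above 30% | Binary, worded as a mean | As 2.13 | As 2.13 | None |

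Two illustrations with assumed values show that the variants differ:

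- If Treg percentage rises by 30% while lymphocytes fall by 20%, the count changes by a factor 1.30 × 0.80 = 1.04. The patient responds on percentage and not on count.
- If 6 of 18 patients double their Tregs and 12 do not change, the mean rise is 6 × 100% / 18 = 33%, above the cut, with only 6/18 = 33% responders.

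**2. Which version the sample size serves**

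Inputs from 2.13: p1 = 0.50, p0 = 0.05, alpha 0.025, power 0.80. Sidedness is not stated there, and two-sided is what reproduces the figure. With the pooled formula and mean rate 0.275:

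n = [2.2414 × √(2 × 0.275 × 0.725) + 0.8416 × √(0.25 + 0.0475)]² / 0.45² = (1.4154 + 0.4591)² / 0.2025 = 17.35, so 18 per arm and 54 in total.

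This matches the plan exactly. (One-sided 0.025 would give 15 per arm, and a continuity correction 22.) At 18 per arm the formula gives 81.7% power. Exact enumeration gives 84% for the uncorrected chi-square test and 75% for Fisher's test.

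**3. What the continuous version would detect**

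The document gives no SD of change, so only a standardised effect follows. With a two-sided t test at 0.025 and 18 per arm (34 degrees of freedom), 80% power needs d = 1.07 before any baseline adjustment.

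The document's cross-sectional figure (60 ± 17 per µL) gives a range once a correlation r between baseline and week 18 is assumed. A 30% rise is 18 per µL, and the SD of change is 17 × √(2(1 − r)):

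| Assumed r | 0 | 0.25 | 0.5 | 0.7 | 0.8 |
|---|---|---|---|---|---|
| Power, t test on change | 47% | 60% | 79% | 96% | 99.5% |
| Power, ANCOVA | 79% | 82% | 90% | 98% | 99.8% |

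**4. Efficiency under two models that both fit 50% versus 5%** (18 per arm, two-sided 0.025)

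*Uniform shift.* Log change is normal with placebo median zero and a Rapamycin median of +30%. Then SD = ln 1.3 / 1.645 = 0.2624 / 1.645 = 0.16, d = 1.645, and the noncentrality is 1.645 × √(18/2) = 4.93.

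*Split population.* The SD is the same, but 53% of treated patients shift by +60% and the rest do not change. The responder rate is then about 50% (simulation).

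| Model | t test | Wilcoxon | Chi-square | Fisher |
|---|---|---|---|---|
| Uniform shift | 99% | not computed | 84% | 75% |
| Split population | 81% | 68% | 85% | 75% |

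**5. How the two can part**

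Take a uniform shift of +20% with SD 0.16. The responder rate is about 31%. Power is 86% for the continuous test, against 40% (chi-square) or 26% (Fisher) for the responder comparison. The same data could well succeed on 2.9 and fail on 2.13.

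**The case against.** The strongest defence is that 2.13 and 2.14 agree with each other. Hypotheses, error rates, sample size and the one analysis that names Tregs are all in responder terms, so 2.9 may merely name the variable and time points without its summary measure. That limits how open the choice is, and a reader should not infer that the plan leaves the primary claim wholly free. It does not remove the conflict: 2.9 is the section that defines outcomes, and it calls a change in number primary.

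Three stronger readings are tempting and are not supported:

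- **That the 2.9 outcome has no planned test at all.** The paragraph on lymphocyte subsets could be read to cover Tregs, and the full protocol and SAP are not shown. What can be said is that no primary test is explicitly assigned to it here. The responder comparison has no named test either.
- **That the responder analysis wastes power.** This needs an SD and a distribution of change that the document does not give. Under the split population the t test falls slightly below chi-square, and Wilcoxon falls below both responder tests.
- **That the trial is underpowered as planned.** The responder sample size reproduces and reaches its stated power by the pooled formula.

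It is also fair that keeping the 2.9 outcome favours the version that currently has no hypothesis or sample size.

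**Conclusion.** The contradiction stands on the text alone and needs no assumption: sections 2.1 and 2.9 name one primary outcome, and 2.13 and 2.14 use another. It is a conflict between statements, not detail left to an SAP. The response definition conflicts in three further respects: number or proportion, the form of the inequality, and mean or per-patient. Only the responder version is tied to a hypothesis and to the 18 per arm.

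The efficiency argument is secondary and conditional. The continuous test gains about 15 points over chi-square (99% against 84%) and 24 over Fisher (99% against 75%) if every treated patient shifts alike. It gains nothing over chi-square (81% against 85%) if about half respond strongly. The article's Discussion says the size of the Treg increase in ALS is unknown, so neither pattern can be presumed. The case for correcting the text therefore rests on the conflicting definitions, not on power.

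**What to change.** Before unblinding, name one primary outcome and make 2.9, 2.13 and 2.14 agree with it (2.1 as well if the responder version is chosen). State whether Tregs are measured as absolute count or as percentage. Give one patient-level response rule, a rise of at least 30%, and remove the word mean from it.

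Suggested choice: keep the 2.9 outcome, analysed as log(week 18 / baseline) by ANCOVA with baseline log Treg and the ΔFS stratum, each dose against placebo at 0.025. Report it as a ratio of geometric means, with the responder proportion as supportive. Section 2.13 should then keep its responder calculation as the basis for 54 and 63. It should add what the continuous test detects at 18 per arm: about d = 1.07 for 80% power, two-sided 0.025, before baseline adjustment.

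Making the responder proportion primary and rewriting 2.1 and 2.9 would also remove the contradiction, and it leaves 2.13 intact.

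**Cost.** No new data are needed, because baseline Treg values and the ΔFS stratum are already collected. The suggested choice takes more than rewording: 2.13 needs the added statement, and a full power claim would need an SD of change from outside this document. The headline result becomes a mean ratio instead of a response rate, which is still reported.
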